### Study aims and approaches

#### Aim 1

Increase the capacity of rural libraries to deliver evidence-based health promotion programs

Capacity building will start pre-program implementation to get the libraries ready for implementation and will continue throughout implementation. We will provide the 20 librarians with technical assistance on program implementation and $5,000 stipends to support program implementation. Librarians will be divided in two groups based on the randomization, a SIU group and a Combined group and will attend trainings and webinars with their group. We will hold two 60-minute trainings for the SIU program and an additional 60-minute training for the Combined program prior to program implementation. All librarians will receive a SIU Toolkit that provides information on how to set up and deliver a group-based walking program as well as handouts for participants. Librarians in the Combined Program will be given a facilitator guide and curriculum for the Change Club and handouts for participants. Additionally, the Change Club groups will be awarded $5,000 after submitting a budget for use of the funds. We will hold monthly webinars to provide an opportunity for the librarians to learn from and support each other as they plan for and implement the programs. The research team will be available via phone calls or email to librarians throughout the study for questions or individualized support as needed. Each librarian will complete the Public Health Professional Competency Assessment [49] prior to the trainings and at the end of the two-year study.

#### Aim 2

Compare the effects of a group-based walking program with a combined group-based plus civic engagement program on physical activity, cardiovascular fitness, and collective efficacy among rural residents.

#### Sub-aim 2a

Identify key mediators between the intervention program effects and change in physical activity, fitness, and collective efficacy.

The objective for Aim 2 is to determine the amplified effects of the combined program on outcomes. Our working hypothesis is that participants in the Combined program will have greater improvement in outcomes compared with SIU program alone because participants in the Combined Program will engage in activities directed at individual, social, and community factors.

### Participants

Librarians, with assistance from the research team, will recruit 15–20 participants. Inclusion criteria are age 18 or older, inactive (defined as engaging in physical activity < 3 days per week), ability to walk for at least 20 min, living within the rural community served by the local library, and ability to travel to the local library/location of walking group. Each potential participant will complete the Physical Activity Readiness-Questionnaire (PAR-Q) [50] as part of the screening process to ensure that they are able to participate in walking groups. If the potential participant answers “yes” to any PAR-Q question, they will be asked to obtain healthcare provider authorization to participate. Based on our prior experience in similar populations and settings, we anticipate that this will be non-limiting to recruitment, while ensuring human subject protection. Exclusion criteria include participation/intention to participate in other lifestyle modification program(s), cognitive impairment, inability to communicate due to severe uncorrected hearing loss or speech disorder, and/or severe visual impairment (if precludes completion of assessments and/or intervention).

Recruitment methods will include fliers/postcards/business cards and bookmarks placed at community locations, such as grocery stores, banks, and retail establishments; word of mouth; radio and/or newspaper ads; and press releases sent to local newspapers. Fliers/postcards/business cards or information as worded on the fliers /post cards/business cards may also be posted on the library or city/town government websites and included in printed and electronic versions of library or community organization newsletters.

### Interventions

The Socioecological Model and Social Cognitive Theory serve as the theoretical foundation for both SIU and the Change Club. We hypothesize that program effects are mediated by increased self-efficacy, social support, group cohesion, and perceived environment resulting in increased physical activity, fitness, and collective efficacy (belief in group capability to achieve goal) [51]. Rural librarians will lead the group walk for SIU, and the group walk and Change Club session for the Combined program. After six months, group walks and Change Club sessions will be peer-led to enhance sustainability. The programs will run for two years.

### Step it up!

Group walks will occur weekly for 60 min. Participants will progressively build up to walking for 45 min at a brisk pace. The first walk will start with setting group norms, building rapport, and developing Specific Measurable Attainable Relevant Timely (SMART) physical activity goals and a short walk. For the next four weeks, the walk will start with a check-in, followed by a 30-minute walk and end with brief stretching. Thereafter, the walks will start with a check-in followed by a 45-minute walk and end with brief stretching. The librarian will use behavior change strategies (Table 1) and will use the spirit of motivational interviewing when talking with participants about behavior change. Each group will create a group name and be given group t-shirts. Each participant will be given a Fitbit Inspire for monitoring and motivation.

**Table 1 Tab1:** Step it up! socioecological & behavior change theory-based strategies

Strategies	Underlying Theoretical Concepts	Empirical Rationale Impact on Study Outcomes
***Individual Domain***		
Discuss feelings regarding exercise experiences	• Commitment • Supportive relationships • Emotional & informational support	Increases group cohesion, social support, exercise adherence [52–55]
Discuss substituting walking for sedentary behavior	• Emotional & informational support	Increases self-efficacy, social support, adherence [52, 56]
Establish goals	• Self-control	Increases self-efficacy, exercise adherence [52, 56]
Fitbit log	• Self-monitoring • Self-reinforcement	Increases self-efficacy, exercise adherence [52, 56]
Emphasize positive benefits	• Physiologic responses • Consciousness raising • Intrinsic motivation	Increases self-efficacy, exercise adherence [52, 54, 57]
Participatory	• Autonomy	Increases self-efficacy, exercise adherence [52, 54, 56, 57]
***Social Domain***		
Positive feedback from group leader	• Positive reinforcement	Increases social support, self-efficacy, group cohesion, exercise adherence [52–54, 57, 58]
Positive feedback from group members	• Social persuasion • Emotional & informational support	Increases self-efficacy, group cohesion, exercise adherence [52, 53, 55, 58, 59]
Exercise together as group	• Modeling experiences • Mastery experiences	Increases self-efficacy, collective efficacy, exercise adherence [52]
Group t-shirt	• Group identity	Increases group cohesion & connectedness [52, 53, 59]

### Combined program

The SIU group walk will be implemented as described above. The group will meet for the Change Club for 30 min after the group walk. The Change Club curriculum has been revised to be implemented in 30-minute sessions and to focus on walkability. The first month topics include building group rapport and identity and establishing group norms, as well as assessment of community walkability assets (Table 2). Months 2–3 focus on change objective identification (e.g., improve trail access), identification of potential partners, and action planning, including delineating benchmarks. The remaining three months, the Change Club will execute the action plan to implement the change, overcoming barriers and challenges. Each Change Club will receive $5,000 upon submitting a proposed budget.

**Table 2 Tab2:** Socioecological aspects of change club curriculum

	*Social Domain*	*Community Domain*
Month 1: Unity & Togetherness	Building rapport; establishing purpose; deciding group name & expectations	Community walking tour; discussing assets, barriers, resources
Month 2: Community Needs	Gaining social support strategies; defining purpose & goals for group	Interviewing local leaders; identifying town needs
Month 3: Next Steps	Leadership skills; identifying connections & strengths of members	Developing action plans; delegating tasks & action items for group members
Ongoing	Overcoming sabotaging related to physical activity	Executing action plan; reviewing progress, benchmarks, accomplishments

### Data Collection

Data will be collected at four timepoints (baseline and 6, 12, and 24 months) by trained research staff. Data collection events will be scheduled at each library at each of the timepoints. The SPIRIT flow diagram (Fig. 1) provides the timing of the intervention and assessments for the trial.

**Fig. 1 Fig1:**
[figure not shown]
Schedule intervention and assessments

### Primary outcomes

#### Physical activity

Physical activity will be assessed with an ActiGraph GT3X + accelerometer (ActiGraph Corporation, Pensacola, FL, USA), worn on the non-dominant wrist for seven consecutive days. Raw accelerometer data collected at 30 Hz will be processed into physical activity metrics using a machine-learned random forest classifier specifically designed and validated for assessing movement behaviors in free living adults [59]. The random forest classification model uses features in the raw acceleration signal to classify each 10 s window (epoch) as sedentary (lying or sitting still), stationary plus (active sitting, standing still, active standing), walking, or running. Predictions for each 10 s period will be smoothed using a modal filter spanning two lead and two lag epochs. In the current study, time spend in moderate-to-vigorous intensity PA will be defined as the sum of daily time spent walking and running. Non-wear periods will be identified by summing the 10-sec windows in which the standard deviation of the acceleration signal vector magnitude is < 13 mg for > = 30 consecutive minutes [60]. The participants accelerometer data will be included in the analyses if they have ≥ 5 days (with at least 1 weekend day) in which wear time is 10 h or longer [61].

#### Cardiorespiratory fitness

The six-minute walk test will measure cardiorespiratory fitness [62]. Participants will walk as quickly as they can on a marked route for six minutes. Distance will be measured in meters.

#### Collective efficacy

The Collective Efficacy Scale will be used to measure collective efficacy [63]. This survey has two subscales- informal social control which has four questions and statements that respondents rate on a 5-point Likert scale from very 1 = likely to 5 = very unlikely and social cohesion and trust, which has four statements that respondents rate on a 5-point Likert scale from 1 = strongly agree to 5 = strongly disagree.

### Secondary outcomes

We will measure height, weight, waist and hip circumference, blood pressure, and resting pulse. Each measurement will be taken twice. Participants will complete surveys that include individual, social, and community level questionaries (Table 3).

**Table 3 Tab3:** Secondary outcomes, self-report surveys

Outcome	Measure	Number of Questions	
***Individual Level***			
Demographics	Demographics (e.g., age, gender, race/ethnicity)	9	
General Health	SF-36 [65] and BRFSS [66]	13	
Physical Activity	International Physical Activity Questionnaire [67]	27	
Physical Activity Self-Efficacy	Self-efficacy Exercise Behaviors Scale [68]	5	
***Social Level***			
Group Cohesion and Connectedness	Physical Activity Group Environment Questionnaire [69]	17	
Social Support	Social Support for Exercise Scale [70]	13	
Collective Efficacy	Collective Efficacy Scale [64]	8	
Mobilization	Mobilization Scale Individual [71]	8	
***Community Level***			
Civic Engagement Attitudes	Civic Engagement Scale [72]	14	
Social Norms	Social Norms for Physical Activity [73]	5	
Walking Environment	Neighborhood Environment Scale [74]	8	
Greenspace Exposure	The People and Nature Survey [75]	3	

BRFSS: Behavioral Risk Factor Surveillance Survey. SF-36: Short Form 36

### Sample size calculation

Results of multiple studies have shown that walking group interventions have small to large effects on physical activity. What is unclear is how much advantage can be gained by combining the walking group and civic engagement interventions. To be conservative, we chose to power this study to detect small effect sizes (Cohen’s d ~ 0.20). We calculated the minimum detectable effect (MDE) for the primary cross-level interaction effect testing whether outcome changes across time differs between intervention groups. MDE was estimated using a multi-level framework using Optimal Design software [75] for the planned intention-to-treat (ITT) analyses for the primary outcomes. Multi-level models were used for power analyses using a range of ICCs and all power analyses assumed alpha = 0.05, power = 0.80, continuous normal outcomes, complete cases, two intervention groups, and four time points (baseline-24 months). We estimate that approximately N = 150 participants per intervention group will allow us to detect effect sizes in the small range (Cohen’s d = 0.15-0.25). Given an expected attrition rate of approximately 10% per year, we will recruit 175–200 participants per arm.

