**Methods:**

We will conduct a comparative effectiveness study of a group-based walking (standard approach) versus a group-based walking plus civic engagement program (combined approach) aimed at enhancing walkability to increase physical activity among rural adults. Key mediators between the program effects and change in outcomes will also be identified. Finally, we will evaluate program implementation, conduct a cost effectiveness evaluation, and use a positive deviance analysis to understand experiences of high and low changers on key outcomes. Twenty towns will be matched and randomized to one of the two conditions and our aim is to enroll a total of 350–400 rural residents (15–20 per town). Study outcomes will be assessed at baseline, and 6, 12, and 24 months.

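### The lower ends of the recruitment ranges (175 per arm, 15 per town) do not cover the stated two-year attrition, and 15 in every town falls short of the 350 minimum

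*Protocol article*

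**What the plan says.** The Sample size calculation section of the protocol article gives the number on which power rests: "We estimate that approximately N = 150 participants per intervention group will allow us to detect effect sizes in the small range", with the range given as "Cohen’s d = 0.15-0.25". The conditions are that "all power analyses assumed alpha = 0.05, power = 0.80, continuous normal outcomes, complete cases, two intervention groups, and four time points (baseline-24 months". Clustering enters only as "Multi-level models were used for power analyses using a range of ICCs", without values. The section then allows for dropout: "Given an expected attrition rate of approximately 10% per year, we will recruit 175–200 participants per arm".

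Two other places set recruitment numbers. The Methods part of the Abstract says "our aim is to enroll a total of 350–400 rural residents (15–20 per town", for 20 towns randomised in matched pairs, hence 10 towns per arm. The Participants section says that librarians, helped by the research team, "will recruit 15–20 participants". It gives no total and no per-arm figure.

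**The concern.** A recruitment range says that any number within it is acceptable. Its lower end should therefore still deliver the number on which power was calculated, after the dropout that the plan itself expects. Here the dropout rate is annual and follow-up lasts two years, so the allowance has to cover both years. A lower end of 175 looks too small for that.

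The per-town range raises a second question. Fifteen in each of 20 towns is not 350. It is also exactly 150 per arm, the power number with no allowance for dropout. The per-town figure is the only one in the Participants section, so it is the one a site is likely to work to. If both lower ends stand, the trial could recruit within a stated range and still finish with fewer complete cases than its power statement assumes.

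**Working it through.** **Inputs, all from the protocol article.** Complete cases per arm: 150. Attrition: about 10% per year. Follow-up: 24 months. Recruitment: 175–200 per arm, 350–400 in total, 15–20 per town. Towns: 20, so 10 per arm.

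**1. Attempt to reproduce 175–200 from 150.** The required number is N / (1 − d), where d is total attrition.
- One year only, d = 0.10: 150 / 0.90 = 166.7, so 167.
- Two years compounded, d = 1 − 0.9² = 0.19: 150 / 0.81 = 185.2, so 186.
- Two years added, d = 0.20: 150 / 0.80 = 187.5, so 188.

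The two-year answer, 186–188, lies near the middle of the stated range (midpoint 187.5). No correct form gives 175. The nearest is the mistaken form N × (1 + d), which gives 150 × 1.19 = 178.5 and 150 × 1.20 = 180. For 175 to leave 150, total attrition would have to be 1 − 150/175 = 14.3%, or 1 − √(150/175) = 7.4% per year, not 10%.

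**2. Complete cases left at 24 months.**

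| Recruited per arm | × 0.81 | × 0.80 | Against 150 |
|---|---|---|---|
| 150 (15 in every town) | 121.5 | 120 | short by about 28–30 |
| 175 (stated lower end) | 141.75 | 140 | short by about 8–10 |
| 190 (19 in every town) | 153.9 | 152 | met |
| 200 (stated upper end) | 162 | 160 | met |

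**3. Do the totals agree?** 20 × 15 = 300; 20 × 20 = 400; 350 / 20 = 17.5. The upper ends match. The lower ends differ by 50 participants. The requirement in step 1 is 2 × 186 = 372 to 2 × 188 = 376 in total, or 18.6 to 18.8 per town.

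**4. Effect on power.** The 150 itself cannot be reproduced, because the article gives neither the ICC values nor the within-person correlation. As an assumption, take exactly 80% power at 150, two-sided 0.05 and no clustering. Power at n completers is then Φ((1.960 + 0.842) × √(n/150) − 1.960):
- n = 141.75: 78%
- n = 121.5: 71%
- n = 162: 83%

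**5. Effect on the minimum detectable effect (MDE).** With 10 towns per arm and m completers per town, the MDE is proportional to √((1 + (m − 1) × ICC) / (10m)). Relative to m = 15 (150 per arm), over an assumed range of ICCs and ignoring any change in degrees of freedom:

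| ICC (assumed) | 141.75 per arm | 121.5 per arm |
|---|---|---|
| 0 | +2.9% | +11.1% |
| 0.01 | +2.5% | +9.7% |
| 0.02 | +2.2% | +8.6% |
| 0.05 | +1.6% | +6.4% |

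The relative loss shrinks as the ICC rises, because the number of towns is fixed.

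**The case against.** The strongest reply is that the plan states ranges and that most of this one works. Its midpoint is almost exactly the number required, and its top leaves 160–162. A reader might infer that the recruitment targets as a whole fail to deliver 150 completers. The documents do not support that: only the part of the range below about 186 falls short.

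A reader might also infer that 350–400 in total and 15–20 per town contradict each other outright. They do not. Any total from 350 to 400 means an average of 17.5 to 20 per town, which lies inside 15–20, and some towns may stop at 15 if others reach 20. The 120–122 figure arises only if every town in an arm stops at 15, which would also breach the per-arm and total aims. The research team assists with recruitment, so someone can watch the total.

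Next, complete cases are an assumption of the power calculation and not a rule of the analysis. The Data management and analysis section plans mixed models using all available data, so a participant lost after 12 months still contributes three time points. Counting only 24-month completers therefore overstates the loss. Both the 150 and the 10% are also given as approximate.

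All of this stands and limits the size of the point. It does not remove it. The dropout allowance was added to a complete-case number, and judged on that basis 175 does not follow from the inputs beside it. Nothing in the article says that the total overrides the per-town minimum.

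Finally, it is tempting to add a further loss from accelerometer records that fail the wear-time rule. The article gives no expected failure rate, and a separate allowance is detail that an article may leave to the full protocol, so it is not part of this point.

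**Conclusion.** The point holds for the lower ends only, and it is minor. At the stated attrition, 175 per arm falls about 8 to 10 completers short of 150. That costs about two percentage points of power without clustering, or an MDE 1.6% to 2.9% larger over assumed ICCs of 0 to 0.05. The 15-per-town bound matters more if it were reached everywhere: 300 in total against a minimum of 350, about 71% power without clustering, and an MDE 6% to 11% larger. That is a limiting case and not the expected outcome.

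These figures assume that 10% per year applies in both years and equally in both arms, that power is exactly 80% at 150, and that dropouts contribute nothing, which the planned mixed model makes pessimistic. The ICC values are assumptions. The design, the analysis and the recruitment ceilings are not in question.

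**What to change.** Choose one of two corrections.

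1. **Raise the lower ends so that they agree:** about 19–20 per town, 190–200 per arm and 380–400 in total. At 190 per arm, 152 to 154 remain at 24 months. This edits the Abstract, the Participants section and the Sample size calculation. The maximum of 20 per town and 400 in total is unchanged; the minimum total rises by 30 (380 − 350).

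2. **Keep the present ranges and say what they yield:** state that 175–200 per arm leaves about 140–162 completers at 24 months, that the total of 350–400 governs over the per-town minimum (an average of at least 17.5 per town), and restate the MDE at about 140 per arm. This needs no extra recruitment, only a rerun of the power calculation and a few sentences.

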### Data management and analysis

Survey data will be collected via REDCap, a highly secure and robust web-based research data collection and management system [76]. Anthropometric measurements and 6-minute walk data will be recorded in Excel and accelerometer data will be downloaded into actilife software; these data files will be stored on a secure cloud-based storage system requiring two-factor authentication.

Standard descriptive statistics of frequency, central tendency, and dispersion will be used to describe the sample and standard psychometric analyses (e.g., Cronbach’s alpha) will be used to assess the reliability of all self-report measures. Before formal modeling, we will identify any departures from statistical assumptions (e.g., outliers, skewness). All primary analyses for each aim will be conducted ITT (including all participants who were randomly assigned to condition regardless of percentage of intervention completed). In addition, we will explore adherence-based analyses in which we will compare groups including only participants who completed 70% or more of the intervention after controlling for any covariates related to adherence.

Our primary aim will be tested with a linear mixed-effects (multi-level) modeling approach implemented in the lmer package in R. Within this framework, the level-1 and level-2 models will include within-person (e.g., measures across time) and between-person (e.g., intervention assignment) variables, respectively. An additional level will be added to the model to account for nesting within town. Changes in outcomes across time will be modeled as a fixed time effect and model testing will be conducted to determine how best to represent change in each outcome (e.g., linear versus nonlinear). Intervention effects will be examined by specifying fixed-effect dummy variables that compare the intervention groups. Specific hypothesis testing will be by specifying cross-level interactions (time x group contrasts) to determine whether differences across time (e.g., baseline-24 months) significantly vary between intervention groups. Model testing will be used to determine the appropriate random effects structure for each outcome, with the default model including random slopes and intercepts. We will evaluate primary hypothesis tests at traditional significance levels (alpha = 0.05) and use modern methods to control for false discovery rate [77] for post hoc analyses. We will focus interpretation on effect size estimation with accompanying 95% confidence intervals (e.g., Cohen’s d). Model diagnostics (e.g., examining residual/predicted value plots) will be used to confirm statistical assumptions have been met. In the case of violations, more robust alternative models will be employed (e.g., robust mixed-effects models) as appropriate.

We will examine dropout and patterns of missing data to determine mechanisms (missing completely at random [MCAR], missing at random [MAR], or not ignorable) [78]. In the case of outcome data MCAR or MAR, model-based maximum likelihood estimation underlying the mixed-effects modeling approach (described above) will allow unbiased parameter estimation using all available data (i.e., missing data are handled efficiently with no loss of information). In the case of predictor/covariate data MAR, we will employ principled methods of multiple imputation available in several R packages [79] and Full Information Maximum Likelihood estimation for structural equation modeling. In the case of non-ignorable missingness (missingness related to the outcomes under study), pattern mixture modeling [80] a method for identifying and incorporating patterns of missingness due to non-random drop out, will be used.

Mediation hypotheses (sub-aim 2a) will be tested within a structural equation modeling framework in a series of latent growth longitudinal mediation models [81]. The strength of longitudinal mediation approaches is the ability to use prior time points to predict future time points, thereby eliminating many of the interpretational problems in determining causal direction that occur when testing mediation with cross-sectional data [82]. Similar to the mixed-effects models described above, intercepts and slopes across time will be estimated for all longitudinal variables involved in a proposed mediation (e.g., intervention group → social support → physical activity). This model can then be specified to test causal relationships forward in time. Additional models with different, or even the same, time points at each stage can be fit to determine the strength and timing of any mediation effects. Point and interval estimates (95% CIs) of the mediating (indirect) effects of these paths for each outcome and mediator will be estimated. These models will also take into account higher levels of nesting (e.g., towns) and include important covariates as appropriate.

#### Aim 3

Evaluate program implementation and cost-effectiveness

The implementation evaluation is based upon the Consolidated Framework for Implementation Research (CFIR) and the Socioecological Model (SEM). The CFIR, derived through a comprehensive synthesis of the implementation literature [83], has five domains: inner setting, outer setting, characteristics of individuals involved, implementation processes, and intervention characteristics. Together, CFIR and the SEM will guide the assessment and help identify factors influencing implementation and intervention effectiveness. Table 4 outlines the CFIR domains and data sources. We expect a complex set of factors will distinguish high-versus-low change in study process and outcome measures. We will identify what influences the extent to which a library is able to implement SIU or Combined program and participants are able to make and maintain behavior changes. We will identify setting/organization (e.g., organizational culture, leadership) and participant (e.g., resources, priorities) factors that distinguish high/low-change among participants and why. We will identify key organizational and local factors that contribute to sustainability and scale-up [84].

**Table 4 Tab4:** Implementation evaluation

CFIR Domains & Constructs	Measures/Data Sources (Timing)
***Program Characteristics*** Complexity; design; adaptability; sustainability; cost; relative advantage	• Cost analysis • Surveys: librarians (3, 6, 12 months) • Interviews: librarians (6 months) • Observations: walks/sessions, webinars
***Inner Setting*** Climate, relative priority, compatibility, leadership	• Surveys: librarians (3, 6, 12 months) • Interviews: librarians (6 months) • Observations: walks/sessions, webinars
***Outer Setting*** Participant resources, needs, facilitators & barriers; cosmopolitanism; built environment/policy	• Surveys: librarians (3, 6, 12 months), participants (baseline, 6, 12, 24 months) • Interviews: librarians (6 months), participants (high & low changers, 6, 12, 24 months) • Attendance records • Observations: walks/sessions, webinars
***Individual Characteristics*** Knowledge; attitudes & beliefs; personal attributes	• Surveys: librarians (3, 6, 12 months) • Interviews: librarians (6 months) • Observations: walks/sessions, webinars
***Process*** Planning; engaging; executing; reflecting; evaluating	• Surveys: librarians (3, 6, 12 months) • Interviews: librarians (6 months) • Observations: walks/sessions, webinars • Recruitment & retention tracking

CFIR: Consolidated Framework for Implementation Research

We will select a sample of participants in three waves for audio-recorded 40-60-minute semi-structured interviews. In wave 1 we will focus on adoption. After six months, we will identify 10 participants with positive deviance (greater increase in physical activity and improvement in fitness), high changers, and compare them with 10 participants who have lower changes in these outcomes, low changers. Participants will be selected to maximize variation in location, arm, and attendance to ensure greatest learning. In wave 2, we will focus on understanding sustainability. We will select participants with positive deviance at six months who sustained changes at 12 months, and participants with positive deviance at six months but who did not sustain changes. In wave 3, we will select participants who have sustained change for 24 months. Interviews will explore participants’ experiences with the program, asking open-ended questions about participant, program, and contextual factors that influenced engagement, behavior change, and sustainability of changes. Interviews will explore barriers and facilitators for engaging in the program, social influences (e.g., support, cohesion), environmental influences (e.g., perceptions of community, built environment), what was most useful and why, what was liked least and most, and what behavior changes were made and why. For civic engagement, we will also ask about approaches to the identified project.

